### Research need

The EQOLISE study was able to prove that the positive effects for the participants assigned to the IPS group are comparable to findings in the US. However, previous studies did not differentiate between participants with different characteristics and thus no conclusions for subgroups of clients such as persons with new-onset disability benefits can be drawn. After receiving an IV-pension the risk of further chronification of a mental illness increases over time, hence making a successful reintegration into the competitive employment market increasingly difficult.

This study is a randomized controlled trial (RCT) and will investigate the effectiveness of SE for IV-pensioners receiving the IV-pension for less than a year.

### Research question

The main aim of this study is:

(1) To determine if job coaching according to the IPS approach leads to a more successful integration of new IV-pensioners into competitive employment.

In addition, the following issues will be analyzed:

(2) Possible enhancement of quality of life, state of mental health and level of self-esteem by finding competitive employment

(3) Chances of maintaining an employment and increasing the workload, if the participant desires this and has the ability

(4) Cost-benefit equation of job coaching and potential saving schemes as compared to the current handling

(5) Predictors for a successful coaching after receiving an IV-pension

(6) The effect of IPS on stigma variables (perceived public stigma, self-stigma, stigma stress) and recovery orientation

(7) Stigma variables and recovery orientation as predictors of finding competitive employment during IPS

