The stigma associated with psychiatric disorders can have a major negative impact on individuals with mental illness. Stigma comes in two forms [10]. First, members of the general public, for example employers, can endorse negative stereotypes about people with mental illness and discriminate against them, e.g. not inviting persons with mental illness for job interviews. This is referred to as public stigma. Second, self-stigma occurs if people with mental illness agree with those negative stereotypes and turn them against themselves, undermining their self-esteem, self-efficacy and motivation to pursue life goals such as employment [11]. People with mental illness can also suffer from stigma as a stressor if they perceive stigma as a potential harm that exceeds their coping resources [12,13].

There are two main reasons to examine stigma variables in the context of IPS [14]: (i) fear of public stigma as well as self-stigma may stop people from seeking competitive employment, therefore increased levels of stigma variables could predict less positive IPS outcomes; (ii) re-entering the workforce and the associated social roles and contacts might lead to an increased perception of social inclusion among people with mental illness, resulting in less self-stigma, perceived public stigma as well as stigma-related stress; therefore stigma variables can be assessed as secondary outcomes of IPS.

The traditional approach in rehabilitating people with mental illness has been *first train*, *then place*[15]. In this approach possible difficult situations concerning the employment are trained beforehand. After training these situations the person is placed in competitive employment. Practicing the various scenarios which could occur in the future employment is useful, but the situations in real life are generally much tougher than expected and differ from the trained situations. In many cases the job was chosen for the client, and not by the client, and was thus not suited to the client`s needs and preferences [1]. *First train*, *then place* has drawbacks, as people become ill and are not able to hold their jobs for a long time [16]. In consequence many of the people treated by this approach are only able to work in a sheltered workplace [17].

As frontline services to integrate IV-pensioners into the competitive employment market are almost non-existent, two problems emerge.

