### Plan of analysis

This study aims to determine, whether job coaching according to IPS enables the successful integration of IV-pensioners into competitive employment.

The total N of this study is 250 participants. Through a Bernoulli randomization the participants are assigned to either the control or the intervention group.

The intervention’s effectiveness is tested by interview based instruments (in total 16 questionnaires). Binary, nominal and interval-scaled data are collected.

A two-factor analysis of variance with the two factors *group* (intervention versus control group) and *outcome* (employment yes/no) will be conducted to control the effectiveness of the intervention. The main criterion of the two-factor analysis will be the quantity of jobs received.

As parameters vary on more than one level a simultaneous comparison in a multilevel model is carried out.

Moreover, the study contains two group comparisons. The persistence of being employed or not in both groups is examined with help of a Cox-regression.

A significance level < 0.05, thus, a confidence interval of 95% is to be achieved.

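### Aim 2 words well-being gains as caused by finding a job, a non-randomised state; the causal result should come from the randomised arms, and the job analysis should be reported as an association

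*Protocol article*

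**What the plan says.** All places are in the protocol article.

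- **Research question, item (2):** "Possible enhancement of quality of life, state of mental health and level of self-esteem by finding competitive employment". The gain is attributed to obtaining work.
- **Research question, item (6)**, by contrast, is framed on the randomised intervention: "The effect of IPS on stigma variables (perceived public stigma, self-stigma, stigma stress) and recovery orientation". Quality of life, mental health and self-esteem are not in that item or in any other item framed on the arms.
- **Recruitment and design** and **Plan of analysis** set up two factors, group and employment yes/no. The second section says that the analysis of variance with the factor "employment yes/no) will be conducted to control the effectiveness of the intervention". It then names the dependent quantity: "The main criterion of the two-factor analysis will be the quantity of jobs received".
- **Plan of analysis** also states "The intervention’s effectiveness is tested by interview based instruments (in total 16 questionnaires", and mentions a multilevel model and a Cox regression. None of these is tied to aim 2.
- **Background, on direction:** self-stigma acts by "undermining their self-esteem, self-efficacy and motivation to pursue life goals such as employment", and on stigma and IPS, "therefore increased levels of stigma variables could predict less positive IPS outcomes". The same section reports patients saying that competitive work raises self-esteem and quality of life. **Research need** adds that chronification makes reintegration harder. Item (7) lists "Stigma variables and recovery orientation as predictors of finding competitive employment during IPS".
- **Table 1:** the quality-of-life profile (LQoLP), the symptom checklist (SCL-90-R), the self-esteem scale (RSES) and job status are all collected at T0 to T4.

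**The concern.** Randomisation balances the arms. It does not balance people who find work against people who do not. If participants in better mental health, or with higher self-esteem, are likelier to get a job, they will score better later whether or not the job did anything. A contrast by employment status then shows a gain that aim 2, as worded, would credit to work.

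There is a second, conditional problem. If employment were kept in the model when the arms are compared on these scores, the group effect would be conditioned on a consequence of IPS and would no longer be the randomised effect.

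At stake is a secondary conclusion with policy weight: that competitive work improves well-being in new pensioners. The main question, whether IPS leads to more competitive employment, is not touched by this point.

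**Working it through.** The article gives no figure for aim 2, so there is nothing to reproduce. The check is a comparison of the texts, then an illustration of size.

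**Texts side by side.** Item (2) has a job as the exposure; item (6) has IPS. Both are in one list, so item (2) is not simply shorthand for an effect of IPS. The article describes the path from job to well-being (Background). It also describes paths from self-stigma through self-esteem and motivation to the pursuit of work (Background), and from chronification to failed reintegration (Research need). With both directions in play, a difference between employed and non-employed participants does not identify either.

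**Illustration.**

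- From the article: 126 and 124 participants, two-sided 0.05.
- Assumed, not in the article: job rates of 40% (IPS) and 20% (control) at average health; correlation 0.6 between true baseline health and the final score; reliability 0.8 of the measured T0 score; odds ratio (OR) for a job of 1 to 2 per SD of better baseline health.
- True effect of work, and of IPS, on the score: zero. 3,000 runs per row.

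| OR per SD | Employed minus non-employed (SD) | False positives, group and employment in model | Employment effect after T0 adjustment (SD) | False positives after T0 adjustment | False positives, randomised arms only |
|---|---|---|---|---|---|
| 1 | 0.00 | 5% | 0.00 | 5% | 4.5% |
| 1.25 | 0.12 | 16% | 0.03 | 5% | 5.1% |
| 1.5 | 0.22 | 38% | 0.05 | 6% | 5.1% |
| 2 | 0.36 | 79% | 0.08 | 11% | 4.7% |

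**Hand check of the size.** The employed and non-employed differ in baseline health by roughly ln(OR) SD, and the final score carries 0.6 of that: 0.6 × ln(1.25) = 0.13, 0.6 × ln(1.5) = 0.24, 0.6 × ln(2) = 0.42. This is a slight overestimate of the simulated 0.12, 0.22 and 0.36, as expected when job rates differ between arms.

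**Hand check of the error rate.** Expected number employed is 0.40 × 126 + 0.20 × 124 = 75.2, leaving 174.8. The standard error is √(1/75.2 + 1/174.8) = 0.138 SD. The ratios 0.12/0.138, 0.22/0.138 and 0.36/0.138 (unrounded inputs) are 0.89, 1.62 and 2.64, giving rejection rates of about 14%, 37% and 75%, close to the simulated 16%, 38% and 79%.

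**Yardstick.** The Sample size section plans to detect 0.42 SD. The largest spurious difference here is 0.36/0.42 = 86% of that.

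**Group effect, only if employment is kept in the model.** A separate simulation used job rates of 38.9% and 20% and correlations of 0.2 to 0.4 between well-being and latent employability (all assumed), with no T0 score and no true effects. The IPS effect was shifted by -0.06 to -0.13 SD and was significant in 8% to 18% of runs.

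**The case against.** The strongest objection is that the article never assigns a model to aim 2. The criterion named for the two-factor analysis is the quantity of jobs. The sentence about the 16 questionnaires speaks of the intervention's effectiveness, which could well mean a comparison of arms. The model for a secondary aim belongs in an analysis plan that is not shown. Aim 2 is hedged by its first word, and a gain suggests change from T0, which is collected.

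Much of this stands, and it rules out three stronger readings that a reader might infer:

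- **That the two-factor analysis will be run on LQoLP, SCL-90-R and RSES, so the IPS effect on them will be distorted.** The article does not say so. The distortion follows only if employment is in that model.
- **That the plan expects the reverse direction.** It entertains both. Item (7) covers only stigma and recovery orientation. For self-esteem and mental health the reverse path is background reasoning, and for quality of life it is not stated.
- **That false positives of 66% to 100% are to be expected.** Such rates (spurious 0.33 to 0.67 SD) arise in the separate simulation above, which rests on assumed job rates and correlations and leaves out the T0 score.

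What the objection does not remove is the wording of the aim. The article itself fixes a causal statement about a non-randomised state, lists no arm-based aim for these outcomes, and declares employment an analysis factor. A later analysis plan would inherit all three.

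**Conclusion.** The point holds as a fault in how aim 2 is framed, not as proof that a particular wrong model will be fitted. Followed as written, the aim invites a causal conclusion from a confounded contrast.

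The size depends on assumptions: 0.12 to 0.36 SD and 16% to 79% false positives without T0 adjustment for odds ratios of 1.25 to 2 per SD, no bias at an odds ratio of 1, and 5% to 11% false positives once T0 is in the model. The direction needs only that healthier participants are likelier to find work. T0 adjustment helps greatly but is not a cure, because the score is measured with error and selection may act through things not measured. The comparison of randomised arms kept its nominal error rate throughout. This should be corrected, at the weight of a secondary aim.

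**What to change.** 1. **Causal result.** Test LQoLP, SCL-90-R and RSES by randomised arm, adjusted for the T0 score, without employment as a factor. The multilevel model already mentioned in Plan of analysis may well accommodate this.
2. **Aim 2.** Reword it as the association of competitive employment with later quality of life, mental health and self-esteem.
3. **Analysis of that association.** Employment must precede the outcome, and the adjustment must use the score measured before the job began (T0, or the last visit before job start). One way is to take participants without a job at a visit, compare those who start one in the next six months with those who do not on later scores, and adjust for the score at the starting visit.
4. **What to avoid.** Do not adjust for the score at the same visit at which employment is recorded, since it may already contain the job's effect. For an immediate, lasting effect d and a correlation r between successive scores within employment status, that model returns about d × (1 − r). With assumed d = 0.40 SD and r = 0.6 this is 0.40 × 0.4 = 0.16 SD.

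**Cost.** Wording and analysis only, since the scores and job status are already collected at T0 to T4. Aim 2 can no longer be worded causally. The arm comparison will also be weak if work is the only route to benefit: with an assumed 20-point difference in job rates, a job effect of 0.3 or 0.5 SD becomes 0.2 × 0.3 = 0.06 or 0.2 × 0.5 = 0.10 SD between arms, with power of about 7% or 12%. A null result there should therefore not be read as showing that work has no benefit.

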## Methods/design

### Time scale

To determine interest in participating in the pilot study ZHEPP, the project has been divided into two phases. The first phase was implemented to ascertain whether enough IV-pensioners were interested in participating in this study. The first phase involved the recruitment of 40 participants and those assigned to the intervention group involved in job coaching. The number of participants was easily reached and the first phase was successfully completed by the summer of 2011. The second phase was then initiated. A further 210 participants had to be recruited to reach the final sample size of 250. This recruitment took place until September 2012. After being assigned to the control or intervention group the participants will be followed up over the next two years. Hence the total duration of the study will be three years and nine months (January 2011 until end of September 2014).

### Recruitment and design

Persons who recently received the approval of the IV-pension were invited to an information event. The aim was to inform about the project as well as the supported employment concept IPS. Additionally the job coaches were introduced to the potential participants.

Those interested in participating in our study had the possibility to register and were invited to an one-on-one dialog for further information. Persons who subsequently wished to participate in the study signed the informed consent and were randomized to one of the two groups (control group or the intervention group). During the following two years the participants will be interviewed every six months concerning their well-being, self-esteem, stigma and recovery variables as well as job status (T_0_-T_4_) (List of instruments see Table 1).

**Table 1 T1:** Overview questionnaire based instruments

**Instrument**	**Variable**	**Perspective**	**Measurement point**				
			**T0**	**T1**	**T2**	**T3**	**T4**
Incentive focus scale	Motivation of participant	P	√	√	√	√	√
Client Sociodemographic and Service Receipt Inventory	Sociodemographic facts; medical supply	P/R	√	√	√	√	√
Lacanshire Quality of Life Profile	Quality of Life	P/R	√	√	√	√	√
Symptom checklist 90-revised	Psychological symptoms	P/R	√	√	√	√	√
Rosenberg self esteem scale	Self-esteem	P/R	√	√	√	√	√
Groningen Social Disability Scale	Social role; social disability	P/R	√	√	√	√	√
Global Assessment of Social Disability Scale	Overall psychological disturbance	R	√	√	√	√	√
Internalizes Stigma of Mental Illness Scale	Stigma coping; social drawback	P	√		√		√
Cognitive appraisal	Cognitive appraisal Stigmatization as stressor	P	√		√		√
Perceived Devaluation-Discrimination Questionnaire	Experienced Stigmatization	P	√		√		√
Recovery Assessment Scale	How they feel about themselves and their life	P	√		√		√
Centre für Epidemiological Studies Depression Scale	Depressive symptoms	P	√		√		√
Job discrimination	Experienced discrimination at working place	P	√		√		√
Client Job Status	Working situation	P/JC	√	√	√	√	√
Job Preferences	Job preferences	P/JC	√				
Indiana Job Satisfaction/ Termination Scale	Job satisfaction beginning, while and at the end	P/JC	√	√	√	√	√

*Note*: P: participant, R: Researcher, P/R: Patient by communicating with researcher, P/JC: Patient by communication with job coach; Measurement point: compiled every six month (T0, T1, T2, T3, T4).

The ZHEPP project is a randomized control trial (RCT) with two factors, *group* (intervention versus control group) and *outcome* (employment yes/no).

The participants of the intervention group are supported by a job coach according to the approach of IPS. Those randomized to the control group are not subject to any intervention by our job coaches, but are merely invited to an interview every six months. The catchment area is the canton of Zurich, Switzerland.

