### Interview based instruments and data collection

Based on the EQOLISE study the following instruments (German version) are used to quantify the outcome of the general well-being of the IV-pensioners. The participants are interviewed every 6 months by research workers (T_0_-T_4_).

(1) Incentive Focus Scale (IF): assessment of the participant`s motivation [25]

(2) Client Sociodemographic and Service Receipt Inventory (CSSRI- EU): assessment of sociodemographic facts and the medical supply [26,27]

(3) Lancashire Quality of Life Profile (LQoLP): assessment of the participant`s quality of live [28]

(4) Symptom-Checklist 90-Revised (SCL-90-R): assessment of the participant`s psychological symptoms [29]

(5) Rosenberg self-esteem scale (RSES): assessment of the participant`s self-esteem [30]

(6) Groningen Social Disability Scale (GSDS-II): assessment of social disabilities, fulfil their social role as expected [31]

(7) Global Assessment of Functioning (GAF): brief assessment of social, occupational and psychological functioning of the participant [32]

(8) Recovery Assessment Scale (RAS), 24-item short version: assessment of participant`s feeling towards him/herself and his/her life [33]

(9) Center for Epidemiological Studies Depression Scale (CES-D), German 15-item version: assessment of depressive symptoms [34]

This study will also assess stigma and recovery variables, using the following validated self-report measures administered once a year (T_0_, T_2_ and T_4_):

(1) Internalized Stigma of Mental Illness Scale (ISMI), 29 items [35]

(2) Cognitive appraisal of stigma as a stressor, 8 items [12,13]

(3) Perceived Devaluation-Discrimination Questionnaire (PDDQ), 12 items, measuring perceived public stigma [36]

Additionally, for those who worked at least one day in the last year.

Experienced discrimination at work, 5 items ([name] et al., unpublished). Furthermore, job preferences as well as the participant`s expectation concerning the process of finding an employment will be evaluated in the first interview (T_0_). Every six months (T_0_-T_4_) the current situation of employment and, if applicable, the participant`s satisfaction with his/her employment are assessed.

(1) Client Job Status: statement of the ongoing working situation of the participant

(2) Job Preferences: assessment of the participant`s job preferences

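### Table 1 has the job-status instrument, the apparent source of the main outcome, completed with a job coach, but only the IPS arm has coaches; one common source for both arms must be stated

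*Protocol article*

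**What the plan says.** All of this is in the protocol article.

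- **Recruitment and design, Table 1.** Client Job Status (T0 to T4), Job Preferences (T0) and the Indiana Job Satisfaction/Termination Scale (T0 to T4) are coded P/JC: "P/JC: Patient by communication with job coach". Five other instruments carry a separate code: "P/R: Patient by communicating with researcher".
- **Recruitment and design, text.** "The participants of the intervention group are supported by a job coach according to the approach of IPS". For the other arm: "Those randomized to the control group are not subject to any intervention by our job coaches, but are merely invited to an interview", and that interview takes place every six months. The same section says that participants are interviewed six-monthly on job status among other things; it does not name the interviewer.
- **Interview based instruments and data collection.** The instrument is described as "Client Job Status: statement of the ongoing working situation of the participant". Research workers are named as interviewers in the paragraph that introduces the well-being instruments. No assessor is named for the job instruments.
- **Plan of analysis.** Effectiveness is to be tested with the 16 questionnaires, and Table 1 has 16 rows. "The main criterion of the two-factor analysis will be the quantity of jobs received". A Cox regression on the persistence of employment is also planned.

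**The concern.** The main outcome should come from the same kind of source, asked in the same way, in both arms. Read literally, Table 1 cannot deliver that, because its procedure for job status needs a coach and controls have none. In the IPS arm the coach necessarily knows the allocation and, according to the Background, also helps to find the job. If one arm's jobs are recorded by a different person or route, a difference in recording cannot be told apart from a difference in employment. Neither randomisation nor a larger sample removes it.

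A second weakness does not depend on arm. An instrument about the ongoing situation, given every six months, is a snapshot. A count of jobs and a Cox regression both need every job with its dates.

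**Working it through.** The plan gives no figure on this point to reproduce. The main check sets the statements side by side.

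**1. Is the code deliberate?** P/R exists and is used for five instruments. The three rows that name the coach are exactly the three job instruments. That looks like a choice rather than a stray label.

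**2. Does the instrument feed the main outcome?** The article does not say so outright. However, effectiveness is tested with the 16 listed questionnaires, the main criterion is jobs, and only Client Job Status has the working situation as its stated purpose.

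**3. What are the possible readings for controls?**

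- Coaches complete the form in the IPS arm only, and someone else or no one does so for controls: the source differs by arm.
- Coaches complete it in both arms: the source is the same, but the assessors are intervention staff who know the allocation, and the contact sits badly with the description of the control arm.
- Research workers complete it in both arms: the P/JC code is wrong.

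Each reading requires a change to the text. Only the first implies unequal ascertainment.

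**4. What could unequal capture do? (Illustration.)** Inputs from the article: 126 IPS and 124 control participants, two-sided 5% level. Assumptions not in the article: the outcome is treated as ever employed yes/no, the true rate p is equal in both arms, IPS capture is complete, and a share s of employed controls is captured. Then d = p − ps, and the rejection rate is Φ((d − 1.96·se0)/se1) + Φ((−d − 1.96·se0)/se1), with se0 the pooled and se1 the unpooled standard error.

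Example, p = 0.30 and s = 0.80: d = 0.30 − 0.24 = 0.06. The pooled rate is (126 × 0.30 + 124 × 0.24)/250 = 0.270, so se0 = 0.0562 and se1 = 0.0560. The two terms are 0.186 + 0.001 = 0.187.

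| True rate | s = 0.95 | s = 0.90 | s = 0.80 | s = 0.70 |
|---|---|---|---|---|
| 10% | 5.2% | 5.8% | 8.5% | 13.5% |
| 20% | 5.5% | 6.9% | 13.0% | 24.2% |
| 30% | 5.8% | 8.2% | 18.7% | 37.1% |
| 40% | 6.2% | 10.0% | 26.0% | 51.7% |

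The nominal value is 5%. Nothing in the article fixes p or s.

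**5. How many jobs can a six-monthly snapshot miss?** Assume starts spread evenly between interviews and exponential job length with mean m months. The share that has ended by the next interview is 1 − (m/6)(1 − e^(−6/m)):

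- m = 3: 1 − 0.5 × 0.865 = 57%
- m = 6: 1 − 0.632 = 37%
- m = 12: 1 − 2 × 0.393 = 21%

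The article gives one instrument and one schedule for everyone, so this loss applies to both arms.

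**The case against.** The strongest objection is that P/JC does not settle who assesses controls. All participants are said to be interviewed on job status every six months. The control arm is shielded from intervention by coaches, which is not the same as saying that coaches never collect data from it. P/JC may describe only the IPS route, or be a loose label, and a condensed article may leave such detail to the full protocol. This stands as far as it goes: differential ascertainment is an inference. It does not dispose of the point, because Table 1 positively names the coach as the route. That is a stated rule in conflict with the design, not an omission.

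A reader might go further and infer established detection bias in favour of IPS: coaches know of every placement, while controls lose all jobs that fall between interviews. The documents do not support this. They never say that continuous coach records define the outcome, and the snapshot loss is not confined to controls. The direction is open too: an IPS participant who stops seeing the coach could be recorded less completely than a control at a scheduled interview.

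It would also be too strong to say that jobs between interviews are never captured. The work-discrimination items are limited to people with at least a day of work in the preceding year, the Indiana scale covers termination of a job, and the Cox regression suggests that timing is collected. None of these is named as the source of the main outcome.

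**Conclusion.** The point holds as an inconsistency that affects the main outcome and as a risk of bias, not as demonstrated bias. The job-status instrument is assigned to a person who, on the article's own description, serves only one arm, and no procedure for controls is given. The conclusion assumes that Client Job Status is the source of the main outcome, which the article implies but does not state.

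The direction and size of any bias cannot be derived from the documents. The rejection rates of 5.2% to 51.7% show what assumed control capture of 95% down to 70% would do at true rates of 10% to 40%; they do not estimate this trial's error. The losses of 57%, 37% and 21% likewise rest on assumed job lengths and concern completeness in both arms. The text should be reconciled before the main outcome is analysed.

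**What to change.** Reconcile Table 1 with the description of the arms and with the data-collection section:

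- Code the three job instruments P/R in both arms and name the research workers as assessors.
- At each remaining T0 to T4 interview, have the same research workers ask for every competitive job since the last interview, with start and end dates. Where earlier interviews did not collect this, ask once, retrospectively, back to randomisation.
- Define the main outcome and the Cox regression from this common source. Keep job-coach records as process data or for a sensitivity analysis.

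The cost is a few more questions at interviews that already take place in both arms. Retrospective questions bring some recall error. Recruitment ran until September 2012 and follow-up to the end of September 2014, so some interviews may already have been completed by coaches. The resulting mix of methods cannot be undone and should be reported, by arm and time point.
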